### Data management

Data obtained by the online questionnaires are stored in a password-protected database maintained by an independent data manager. The email addresses of participants, which is the only personal information we obtain, will be stored in a separate database, which is also maintained by an independent data manager and will be destroyed after data collection. Both databases are not accessible by the researchers and the data of the online questionnaires will become available for research purposes when data collection has been completed. The data obtained by the MoodMonitor app are not stored on the participants’ smartphones, but on a remote server, to which the anonymised data are sent through a secured connection. The app data (i.e. mood and energy ratings) are also not accessible by the researchers until data gathering has ended. The independent data manager monitors the data flow. There is no (other) data monitoring committee, due to the minimal burden and risk associated with participating in this study. After the publication of this study’s main results, the data obtained by this study will become available on request. Requests should be sent to [contact] with the topic name MoodMonitor.

### Analyses

The primary outcome is the effect of EMA on depressive symptoms as measured by the CES-D at T6 and T12, comparing both EMA groups with the control group. To test this on all available data, we will conduct a mixed models repeated measures regression analysis, with T6 and T12 CES-D data as the dependent variable, and baseline CES-D scores, group (1, 2, 3), time (T6, T12) and the time*group interaction as independent variables. Effects will be expressed in terms of percentage of variance explained and Cohen’s d (by dividing raw regression parameter point estimates and confidence intervals by the pooled CES-D standard deviation).

For our secondary analysis, we will examine the EMA response rate over time, which gives an indication of response fatigue. Response fatigue will also be analysed by assessing response accuracy, here defined as a declining correlation over time between theoretically associated measures. Literature has shown that mood swings are associated with higher depressive symptoms [23]. Therefore, we will analyse the variance of the EMA and its correlation with the CES-D scores, taking into account the EMA ratings of the two weeks prior to the CES-D (i.e. weeks 5 and 6 for T6 and weeks 11 and 12 for T12). A decreasing variance of EMA ratings (i.e. increasingly stable responses) will result in a decreasing correlation coefficient (*r*) with the CES-D scores if the CES-D scores do not decrease. This might indicate a decline in validity.

We will maintain a family-wise two-tailed *p*-value of .05 using the Holm-Bonferroni method [24]. IBM SPSS Statistics 23 [25] and R [26] will be used for all analyses.

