## Methods

### Study design

This study is a 12-week randomised controlled trial among participants who experience mild to moderate depressive symptoms. The trial consists of three groups: group 1 carries out EMA of mood and completes a retrospective questionnaire; group 2 carries out EMA of how energetic they feel and completes a retrospective questionnaire; group 3 is the control group, which completes only the retrospective questionnaire. The retrospective questionnaire is the Centre for Epidemiologic Studies Depression scale (CES-D) [15], which assesses depressive symptoms. The CES-D is administered at baseline (T0), 6 weeks after baseline (T6) and 12 weeks after baseline (T12).

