### MoodMonitor, a self-monitoring application

Participants in group 1 and 2 install the MoodMonitor application on their smartphones, which conducts EMA of mood and energy level. This app has been developed by the E-Compared consortium [8]. Every day, the participant will receive one notification on his/her smartphone at a random time point between ten o’clock in the morning and ten o’clock in the evening. This notification directs the participant to the question ‘How is your mood right now?’ (group 1) or ‘How energetic do you feel right now?’ (group 2), which the participant can answer on a visual analogue scale from 1 (worst) to 10 (best) with a precision of 1 digit after the decimal point, e.g. 8.1. The notification remains accessible until the question is answered. If a notification remains unanswered, it is replaced when the next notification is sent. The measurement will be time stamped, i.e. the system records the exact time when the participant enters a rating, in addition to the time when the notification was sent. Furthermore, participants are free to provide a rating at any time they want by opening the app. During week 1 and week 12, the participant rates his/her mood three times a day instead of just once, in order to measure mood fluctuations during the day. The entered ratings are instantly visible to the participants on a graph which they can access through the MoodMonitor application.

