### Sample size

For the sample size calculation, we assume that a difference between either EMA group and the control group within the margin −0.25< Cohen’s d <0.25 is clinically negligible. Therefore, a difference between groups of d = 0.25 should reach statistical significance in our analysis. We ran a power calculation in G*Power [27] for a repeated-measures analysis of variance (ANOVA), which is essentially the same analysis as linear mixed modelling when there are no missing values. A total number of 120 participants (40 per group) is required in order to obtain d = 0.25 with three assessment waves, a targeted power of .85, a significance level alpha of .05, and conservative estimations of correlations between measurements (*r* = .65) and variances of the differences between groups (non-sphericity correction epsilon = .8). Expecting 25 % drop-out at T12, we will recruit 160 participants. All participants will be included in the linear mixed model, which is robust for missing data.

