### Implications

This study will give a first indication of EMA reactivity on depressive symptoms. An effect of EMA on depressive symptoms would limit EMA as an instrument, because a change in EMA ratings might be attributed to the EMA itself instead of treatment or other factors. This is of immediate interest to research projects in which participants carry out EMA over longer periods, such as the E-COMPARED project [8]. However, a positive effect would indicate that EMA can be applied as an intervention, e.g. alongside psychotherapy or pharmacotherapy. A negative effect would indicate that it may not be ethical to use EMA as an instrument. If we find indications of response fatigue at T6 and/or T12, we can recommend the optimal period of conducting EMA.

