### Limitations

First, a change in retrospectively measured depressive symptoms could be attributed not only to a change in depression severity, but also to a change in response behaviour. If we find an effect, we can explore changes in response behaviour by testing the CES-D outcomes for measurement invariance [28]. Second, one of our secondary aims is to investigate response rate, but the response rate might be artificially high, because participants are given a monetary reward when they complete 80 % or more of the EMA prompts. This reward is necessary to answer the primary research question, because any effect of EMA can only be shown when participants conduct EMA.

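### The response-accuracy correlation has only two late windows, so by itself it can support a T6-to-T12 statement but not fatigue at T6 or the timing of its onset

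*Protocol article*

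**What the plan says.** The Background section of the protocol article makes response fatigue the second aim and gives it two operationalisations: response rate over time, and correlations with measures of associated constructs. The Analyses section takes them in turn.

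- **Response rate:** "we will examine the EMA response rate over time, which gives an indication of response fatigue". No window is attached to this.
- **Response accuracy:** loss of accuracy is "here defined as a declining correlation over time between theoretically associated measures". The quantity is the correlation of EMA variance with the CES-D, using the ratings from the fortnight before each CES-D: "i.e. weeks 5 and 6 for T6 and weeks 11 and 12 for T12".

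The CES-D is also taken at T0, but no EMA ratings are paired with it. EMA starts in week 1, and its density varies: "During week 1 and week 12, the participant rates his/her mood three times a day instead of just once".

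The Implications section then says: "If we find indications of response fatigue at T6 and/or T12, we can recommend the optimal period of conducting EMA". The Limitations section adds that "the response rate might be artificially high, because participants are given a monetary reward".

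**The concern.** A decline needs an earlier value to decline from. The accuracy correlation has none before weeks 5-6, so its T6 value has no reference. If ratings lose accuracy in the first month and then level off, the T6 and T12 correlations agree in expectation, and this measure shows no fatigue. If a decline between T6 and T12 is found, one contrast cannot say when it began.

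The Implications section does not separate the two fatigue measures. It speaks of fatigue at T6 as well as at T12 and builds a recommendation on duration from it. For the accuracy measure, the T6 part has no stated analysis behind it. At stake is what the trial can say on its second aim. The primary comparison of CES-D between groups is unaffected.

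**Working it through.** **1. The plan's own figure.** The article gives no sample size or precision for the fatigue analyses. Its only calculation is for the primary analysis: "A total number of 120 participants (40 per group) is required in order to obtain d = 0.25 with three assessment waves". It reproduces. With f = 0.25/2 = 0.125, three groups, three waves, correlation .65 and epsilon .8, the noncentrality is 0.125² × 120 × 3 × 0.8 / (1 − 0.65) = 12.86. The degrees of freedom are 2 × 2 × 0.8 = 3.2 and 117 × 2 × 0.8 = 187.2, and the power is .851. Then 120 / (1 − 0.25) = 160. The present point does not depend on these figures.

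**2. What each fatigue measure can show.**

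| | Response rate | Accuracy correlation |
|---|---|---|
| Weeks used | No restriction stated, so 1-12 | 5-6 and 11-12 |
| Contrasts between time points | Any | 2 × 1 / 2 = 1 (T6 to T12) |
| Contrasts ending at T6 | Yes | 0 |
| Can show a loss completed before week 5 | Yes, as a fall in responding | No |
| Can place the onset of a decline | Yes, in principle | No |

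**3. Illustration with assumed correlations.** Suppose the true correlation is .40 in weeks 1-2, .20 in weeks 5-6 and .20 in weeks 11-12. The planned contrast is .20 − .20 = 0. The loss of .40 − .20 = .20 happened before the first window and is not seen.

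**4. Density of the windows.** Scheduled prompts, reading the three-a-day rule as applying to both EMA groups:

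- weeks 1-2: 7 × 3 + 7 × 1 = 28
- weeks 5-6: 14 × 1 = 14
- weeks 11-12: 7 × 1 + 7 × 3 = 28

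A variance from 14 ratings is noisier than one from 28, and noise attenuates a correlation. A simulation assumed a true correlation of .30 between CES-D and log variance, independent ratings and every prompt answered. It gave these observed correlations of variance with CES-D:

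| Assumed between-person SD of log variance | 14 ratings | 28 ratings | Difference |
|---|---|---|---|
| .4 | .198 | .237 | +.039 |
| .6 | .223 | .246 | +.023 |
| .8 | .220 | .237 | +.017 |

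The shift of about .02 to .04 runs upward from T6 to T12, so it works against finding a decline.

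**5. Scale of that shift.** Take 80 EMA completers (2 × 40), with both groups pooled as an assumption. The standard error of a difference between two Fisher-transformed correlations is √(2/77) = .161 if the estimates are independent, and √(2 × 0.5/77) = .114 if they correlate .5. The density shift is therefore small against sampling error, but it is systematic. Even the assumed loss from .40 to .20 is a Fisher difference of .424 − .203 = .221, or 1.4 to 1.9 standard errors. A correlation contrast is a blunt tool in any pair of windows, which argues for a weekly variance trend as the main addition rather than a third correlation.

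**The case against.** **Response rate covers the early weeks.** The article names it first, sets no window for it, and the Implications sentence does not tie fatigue to the correlation. A reader might infer that early fatigue cannot be seen at all, or that no optimal period could be derived. The documents do not support either reading, because response rate can show an early fall and can inform a period. The disclosed effect of the reward limits this measure but does not make a fall over time invisible. Response rate does not replace accuracy, however, since people can keep answering with less care.

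**Nothing is endorsed after a null result.** The Implications sentence is conditional on finding fatigue, and the Analyses section says only that a falling correlation might indicate lower validity. A reader might infer that equal T6 and T12 correlations would lead to long EMA periods being recommended wrongly. The article does not say so.

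**The windows follow a rule.** Ratings are taken from the fortnight before each CES-D, and no EMA exists before T0. This explains the gap but does not supply a T6 contrast. It also means that pairing weeks 1-2 with the T0 CES-D reverses the order used elsewhere. A reference attenuated for that reason could hide a decline.

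**Variance is already named.** The Abstract lists change in the variance of the EMA ratings as a form of reactivity, and weekly modelling detail may sit in a fuller plan. That stands as a reason to treat this as a clarification. It does not alter the fact that the Analyses section fixes the windows of the accuracy measure explicitly.

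**Conclusion.** The point holds for the accuracy correlation and only for it. As fixed in the Analyses section, the measure has two windows, one contrast and none that ends at T6. It cannot show a decline at T6 or before week 5, and cannot place the onset of one. That follows from the definition and needs no assumption about how fatigue develops. The documents give no shape or speed of decline, so the share of a decline that would be missed cannot be quantified.

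The imbalance of 14 against 28 scheduled prompts weakens the one available contrast further. The size of that effect, about .02 to .04 in the correlation, rests on the assumed simulation inputs.

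This concerns a secondary aim with hedged wording. It is a cheap improvement that changes what the trial can conclude about accuracy, not a flaw in the primary analysis.

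**What to change.** **In Analyses:**

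- Add a model of within-person EMA variance by week over weeks 1-12. Use one randomly chosen prompted rating per day in every week, so that weeks 1 and 12 match the rest. Read the trend beside the CES-D course, because the article itself treats falling variance as a sign of lost validity only where CES-D scores do not fall.
- Apply the same selection to the T6-T12 correlation contrast, giving 14 scheduled ratings in each window.
- Optionally add a density-matched correlation of weeks 1-2 with the T0 CES-D, as supportive only. State that these ratings follow their CES-D rather than precede it, so that an attenuated reference could hide a decline.

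**In Implications:** state that the accuracy correlation supports only a T6-to-T12 statement. State also that anything said about fatigue by T6, or about the period of EMA, rests on response rate and the weekly variance trend.

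**Cost:** no new data, assessments or participants. Matching sets aside 28 of the 112 scheduled prompts (2 × 21 + 10 × 7 = 112, of which 12 × 7 = 84 are kept) in these analyses only. There is slightly more secondary analysis and one more test in the Holm family.

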## Abstract

**Background:**

Ecological momentary assessment (EMA) of mental health symptoms may influence the symptoms that it measures, i.e. assessment reactivity. In the field of depression, EMA reactivity has received little attention. We aim to investigate whether EMA of depressive symptoms induces assessment reactivity. Reactivity will be operationalised as an effect of EMA on depressive symptoms measured by a retrospective questionnaire, and, secondly, as a change in response rate and variance of the EMA ratings.

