This study aims to investigate whether EMA of depressive symptoms induces assessment reactivity. First, we will investigate whether EMA of depressive symptoms during a 12-week period has an effect on depressive symptoms measured by a retrospective questionnaire. Secondly, we will investigate whether response fatigue affects the EMA ratings. Response fatigue will be operationalised as response rate over time and correlations with measures of associated constructs. To minimise response burden, participants will monitor only one symptom and 1 to 3 times a day. Because depression is a multidimensional construct [14] we will conduct EMA of two core depression symptoms in two groups, where group 1 monitors mood and group 2 monitors how energetic they feel. Based on the literature we expect a small positive short-term effect of EMA on depressive symptoms.

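### The stated link between falling EMA variance and a falling correlation with the CES-D does not hold in general, and unequal rating windows distort it further, so the correlation criterion can miss or mask response fatigue

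*Protocol article*

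**What the plan says.** The protocol article describes the second form of reactivity in three places.

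- **Abstract, Background:** reactivity is operationalised "secondly, as a change in response rate and variance of the EMA ratings".
- **Background, last paragraph:** "Response fatigue will be operationalised as response rate over time and correlations with measures of associated constructs". Variance is not mentioned here.
- **Methods, Analyses:** response rate over time is one indicator. Response accuracy is the other, "here defined as a declining correlation over time between theoretically associated measures". For this, "we will analyse the variance of the EMA and its correlation with the CES-D scores", using weeks 5 and 6 for T6 and weeks 11 and 12 for T12.

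The Analyses section then gives the reasoning that links the two quantities: "A decreasing variance of EMA ratings (i.e. increasingly stable responses) will result in a decreasing correlation coefficient" "with the CES-D scores if the CES-D scores do not decrease". The reading of such a fall is cautious: "This might indicate a decline in validity".

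The section on the MoodMonitor application sets one prompt a day, but three a day in weeks 1 and 12. Under Implications, the article says: "If we find indications of response fatigue at T6 and/or T12, we can recommend the optimal period of conducting EMA".

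**The concern.** The sentence in the Analyses section is what justifies reading fatigue from the correlation. On the natural reading, each participant contributes one within-person EMA variance and one CES-D score per time point, and r is computed across participants. Such an r measures whether people with more variable ratings also have higher CES-D scores. It does not measure how variable the ratings are on average. A general loss of variability and a fall in r are different events, and neither implies the other.

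The attached condition does not repair this. It concerns the level of the CES-D, and r does not respond to level.

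The T12 window is also sampled more densely than the T6 window because of the three-a-day schedule in week 12. A variance estimated from more ratings carries less noise, which tends to raise r at T12 whether or not accuracy has changed. At stake is whether the accuracy part of the secondary analysis can show what it is meant to show.

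**Working it through.** The plan gives no figure for this rule, so it is tested as a mathematical statement and then sized under stated assumptions.

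**1. Invariance.** For any c > 0 and any constant b, corr(cV + b, Y) = corr(V, Y). In a simulated set of 80 persons, r was 0.4643 with every variance multiplied by 1, 0.75, 0.5 or 0.25, and the same after a constant shift. No assumption about effect size enters here.

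**2. Prompts per window** (MoodMonitor section and Analyses).
- Weeks 5-6: 14 days × 1 = 14.
- Weeks 11-12: 7 × 1 + 7 × 3 = 28.

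**3. A formula for r.** Let C be the standardised CES-D, and let the log of a person's true variance be normal with slope β on C and total variance τ². With m independent normal ratings, all prompts answered, the sample variance has relative noise 2/(m − 1). Let k be the factor by which a person's variance shrinks, independent of C. Then

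r = β / √[exp(τ²) × E(k²)/E(k)² × (1 + 2/(m − 1)) − 1].

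If k is the same for everyone, the ratio E(k²)/E(k)² is 1 and k drops out.

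**4. Effect of the windows.** Assumed: correlation .45 between CES-D and log SD, and spread .3 of log SD. The log variance then has spread .6, so τ² = .36 and β = .45 × .6 = .27.
- m = 14: .27 / √(1.4333 × 1.1538 − 1) = .27 / .809 = .33.
- m = 28: .27 / √(1.4333 × 1.0741 − 1) = .27 / .735 = .37.

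Halving every SD (variance down 75%) changes neither value. With matched sampling r stays at .33. With the planned windows it rises from .33 to .37, with or without flattening.

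**5. Sensitivity to within-day similarity.** Three ratings on one day are unlikely to be independent. In a simulation with the same parameters (every SD halved at T12, 200,000 persons), r moved from T6 to T12 as follows:

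| Within-day correlation | r, weeks 5-6 | r, weeks 11-12 |
|---|---|---|
| 0 | .34 | .37 |
| .5 | .34 | .36 |
| .7 | .34 | .34 |
| .9 | .33 | .33 |

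**6. Direction depends on who flattens.** A second assumed set (β = .3, residual SD .5, so τ² = .34), with the CES-D unchanged and 14 ratings in both windows, gave by simulation:

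| Pattern of falling variance | r at T6 | r at T12 |
|---|---|---|
| Everyone halved | .38 | .38 |
| Everyone to one quarter | .38 | .38 |
| A random half of persons to 20% | .38 | .26 |
| More depressed flatten more | .38 | .00 |
| Less depressed flatten more | .38 | .57 |

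Mean EMA variance fell in every row, and the plan's condition on the CES-D was met in every row. The claimed fall in r occurred in only two of the five.

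**The case against.** Several points on the other side are sound and limit the claim.

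- **Uneven flattening does lower r, as the authors expect.** With the parameters of step 4, if a random half of persons halve their SD, E(k²)/E(k)² = .53125/.390625 = 1.36 and r falls from .33 to .24. Uniform shrinkage can also lower r if part of the rating noise does not shrink. A reader might infer that flatter responding always leaves r unchanged. That holds only for proportional flattening of the whole variance.
- **The correlation is not the only indicator.** A reader might infer that a stable r would be taken as proof of no fatigue. The plan states no such rule. The Analyses section says the EMA variance itself will be analysed, the Abstract names its change as an outcome, and response rate is separate. Nearly flat ratings could be seen there.
- **The recommendation on the EMA period does not rest on r alone.** The Implications section speaks of indications of fatigue in general, and app data run from week 1. Only the correlation lacks a reference before T6.
- **The CES-D has a purpose as an external anchor.** Variability may fall because participants improve. A test of variability alone could count real stabilisation as fatigue, so the anchor should be kept.
- **The interpretation is hedged and the analysis is secondary.** Both are true, but the caution applies to what a fall in r would mean. The preceding claim, that lower variance produces that fall, is stated without qualification.

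What remains is that the stated implication is wrong and the two windows are not comparable as planned.

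**Conclusion.** Wrong as written, and confined to the secondary analysis. Lower EMA variance need not lower the correlation with the CES-D, and the condition on CES-D scores does not make it do so. The criterion can miss or mask response fatigue. The documents do not support saying that it will miss it, or that fatigue would go undetected overall.

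The invariance result needs no assumptions. The sizes do: association .45, log-SD spread .3, normal ratings and full response. The artefact from 28 against 14 prompts is about .03 to .04 in r with independent ratings. It shrinks as ratings from the same day become more alike, and had vanished at a within-day correlation of .9. It is therefore a modest distortion, but it works against finding a decline. The three descriptions of the outcome also differ in emphasis: variance in the Abstract, correlation in the Background, both in the Analyses. This leaves open which of them is the test of fatigue.

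**What to change.** 1. Delete the sentence on decreasing variance, or make it conditional: r may fall if the loss of variability differs between persons in a way that weakens its relation to the CES-D.
2. Name within-person change in EMA variability as the fatigue test, as the Abstract already implies, and align the Background with it. Compare equally sampled windows: week 1 against week 12 (both three prompts a day), or week 12 thinned to one prompt per day when weeks 11-12 are compared with weeks 5-6.
3. Adjust for the person's mean rating and for change in CES-D, so that genuine improvement is not counted as fatigue.
4. Report the T6 and T12 correlations on matched sampling as supportive, with a confidence interval for their difference that allows for the same persons contributing to both.

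The cost is a little more modelling, with no new data. One limitation remains: week 1 has no matching post-baseline CES-D, so the baseline CES-D would have to serve as its anchor. Thinning week 12 also discards ratings, which makes that comparison somewhat less precise.

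### The .85 power is computed at an unadjusted alpha of .05, but the EMA-versus-control comparisons will be tested under Holm-Bonferroni at a smaller first threshold

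*Protocol article*

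**What the plan says.** The Analyses section of the protocol article defines the primary outcome as the effect of EMA on depressive symptoms "as measured by the CES-D at T6 and T12, comparing both EMA groups with the control group". The model is a mixed model for repeated measures on the T6 and T12 scores, with baseline CES-D, group, time and their interaction as independent variables. After the secondary-analysis paragraph the section adds: "We will maintain a family-wise two-tailed *p*-value of .05 using the Holm-Bonferroni method". It does not list the hypotheses that form the Holm family.

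The Sample size section treats as clinically negligible "a difference between either EMA group and the control group within the margin" of ±0.25 in Cohen's d, and concludes that "a difference between groups of d = 0.25 should reach statistical significance in our analysis". The calculation is a repeated-measures ANOVA in G*Power with three assessment waves, "a targeted power of .85, a significance level alpha of .05", a correlation of .65 and epsilon of .8. It gives 120 participants, 40 per group, raised to 160 for 25% drop-out. Multiplicity is not mentioned.

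The Abstract says that the study is powered for a small between-groups effect, with ±0.25 as the margin. The Discussion says that the mixed model analyses can show effects beyond ±0.25.

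**The concern.** The Sample size section ties its power to significance in the planned analysis, for either EMA group against control. That analysis contains at least two such comparisons, and Holm-Bonferroni has no effect unless there are at least two tests. The smallest p-value in the family must then fall below .05/2 = .025, or .05/4 = .0125 if each EMA group is compared with control separately at T6 and T12. The power calculation uses .05. The two sections therefore fix different alphas for the same claim.

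What is at stake is how a null result is read. If readers believe that the trial had 85% power at d = 0.25, a non-significant Holm-adjusted comparison will look like evidence that EMA causes no relevant reactivity. The Implications section draws conclusions about EMA as an instrument, and about the ethics of its use, from whether an effect is found.

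**Working it through.** **Inputs from the Sample size section:** d = 0.25, so f = d/2 = 0.125; k = 3 groups; m = 3 waves; correlation ρ = .65; ε = .8; α = .05; power .85; N = 120; drop-out 25%. **From Analyses:** two EMA-control comparisons, two time points, family-wise .05 two-tailed by Holm.

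**1. Reproducing the plan's figure.** The article does not name the G*Power option. The within-between interaction uses:

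- λ = N·m·f²·ε/(1−ρ) = 120 × 3 × 0.015625 × 0.8/0.35 = 12.86
- df1 = (k−1)(m−1)ε = 2 × 2 × 0.8 = 3.2
- df2 = (N−k)(m−1)ε = 117 × 2 × 0.8 = 187.2

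Power at α = .05 is 85.1%, and 120 is the smallest N that reaches .85. With the same groups and waves, the other options give different totals: 98 for the within factor and 539 for the between factor, both at f = .125. Drop-out: 120/0.75 = 160. So 120 and 160 are reproduced, as one omnibus test at unadjusted .05.

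**2. Changing only alpha, at N = 120.**

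| First threshold | Power | N for .85 | With 25% drop-out |
|---|---|---|---|
| .05 (as stated) | 85.1% | 120 | 160 |
| .025 (two comparisons) | 77.6% | 141 | 188 |
| .0125 (four comparisons) | 69.2% | 160 | 214 |

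The loss is 85.1 − 77.6 = 7.5 points, or 85.1 − 69.2 = 15.9 points.

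**3. The contrasts the analysis tests.** Assumptions: 40 completers per arm, equal SDs (scaled to 1), correlation .65 between all pairs of waves, baseline as covariate, normal approximation.

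- Residual variance at one time point: 1 − .65² = .5775. Residual covariance of T6 and T12: .65 − .65² = .2275.
- Residual variance of the mean of T6 and T12: (.5775 + .2275)/2 = .4025.
- Standard error of a contrast, √(2 × variance/40): .170 at one time point, .142 for the average.
- Standardised effect: .25/.170 = 1.47 at one time point; .25/.142 = 1.76 for the average.

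Unadjusted power at .05 is 31% for a single time point and 42% for the average. Full Holm was then simulated with 400,000 replicates, keeping the correlation that comes from the shared control group:

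| Family | Unadjusted | Holm, d = 0.25 in both EMA arms | Holm, d = 0.25 in one arm only |
|---|---|---|---|
| Two contrasts averaged over T6 and T12 | 42% | 35% | 32% |
| Four time-specific contrasts | 31% | 18% | 16% |

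(Power for a given contrast in an arm with an effect.)

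**4. Detectable d at 85% power, 40 per arm.** Averaged contrast: 0.43 at .05, 0.47 at .025. Time-specific contrast: 0.51 at .05, 0.60 at .0125. Most of the distance from 0.25 is therefore present before any multiplicity adjustment.

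**The case against.** The strongest objection is about attribution. A reader might set 35% beside the stated 85% and blame Holm for the whole difference. The figures do not support that: the averaged contrast has only 42% power at unadjusted .05. The fall from 85% to 42% arises because N was found for an omnibus group-by-time interaction over three waves, whereas the analysis tests EMA-control contrasts on T6 and T12 with baseline as covariate. That is a separate point. The adjustment accounts for 42% to 35%, or 31% to 18%. This stands.

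Second, the Holm family is not defined, and its definition may properly be left to an analysis plan that is not shown. This stands as far as the size of the loss goes, which can only be given as a range. It does not remove the mismatch: any family of two or more tests has a first threshold of at most .025. A single omnibus test at .05 that gates the contrasts would match the sizing alpha, but the article states no such gate.

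Third, because the Holm sentence follows the secondary analyses, a reader might infer that the response-fatigue tests take alpha from the primary comparison. That rests only on where one sentence sits. The section separates primary from secondary, and the fatigue analyses are largely descriptive. The inference is not made here, although a clarifying clause would settle it.

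Fourth, the contrast figures assume 40 completers per arm. All 160 participants enter the mixed model and the 25% loss is expected at T12, so more T6 data may be available. The figures are therefore somewhat pessimistic. With no loss at all (53 per arm) the averaged contrast would have 53% power at .05 and 42% at .025.

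**Conclusion.** The point holds as an inconsistency between two sections. The .85 power is stated at an alpha that the planned analysis does not use for its first rejection. No definition of a Holm family of two or more tests would make the stated figure right.

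On the protocol's own calculation the cost is about 7.5 points (two comparisons) to 16 points (four). For the contrasts themselves, with d = 0.25 in both arms, it is about 7 points (42% to 35%) to 13 points (31% to 18%). These sizes rest on the assumptions listed with the calculation and on a family of two or four tests. Because Holm's later steps are less strict, a given contrast loses somewhat less than under plain Bonferroni when other tests in the family are also rejected.

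A reader might also infer that the sample size was miscalculated. It was not: 120 and 160 follow from the stated inputs. The error lies in what the resulting power is said to apply to.

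**What to change.** - In Analyses, name the primary EMA-control contrasts that form the Holm family, and state that the secondary response-fatigue analyses lie outside it. Whether the primary contrasts are time-specific or averaged over T6 and T12 is the sponsor's choice. The mismatch does not require a change of estimand, and the Discussion refers to both short-term and longer-term effects.
- In Sample size, keep N and restate the power, or the detectable d, for those contrasts at the adjusted alpha, with the assumptions given.
- Revise the statements in the Abstract, Sample size and Discussion that an effect of d = 0.25 can be detected.

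No change to recruitment, design or data collection is needed. The cost is in the claims: the stated power becomes clearly lower, not marginally so, and secondary results carry no family-wise error guarantee.
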